## Abstract

**Background:**

Obstetric cholestasis (OC) is a serious problem in pregnancy. It affects about 4500 women per year in the UK. Affected women develop itching and occasionally jaundice. More importantly, the condition is associated with premature delivery, fetal distress and is believed to be an important cause of stillbirth. However, even now, there is no clear evidence as to whether the most popular treatment, a drug called ursodeoxycholic acid is beneficial to the baby, or even if it is safe in pregnancy. Nor do we know whether planned early delivery of the baby at 37–38 weeks, another popular treatment, does more good than harm. A randomised trial to evaluate both ursodeoxycholic acid and timed delivery is needed but will be complicated and expensive. We plan a preliminary study, Pilot study for a trial of ursodeoxycholic acid and/or early delivery for obstetric cholestasis (Acronym PITCH- **P**regnancy **I**ntervention **T**rial in **Ch**olestasis) trial, to evaluate the feasibility of a larger trial. The trial is funded by the NHS Research for Patient Benefit (RfPB) Programme.

**Methods:**

PITCH is a multi-centre, double blinded, randomised, controlled, factorial design trial. The trial is being run in six UK centres and women with obstetric cholestasis will be recruited for eighteen months. In this pilot trial we aim to collect data to finalise the design for the main trial. This will include measuring trial recruitment rate, including recruitment to each factorial comparison separately. We will also measure the spectrum of disease among recruits and non-recruits and compliance with the four possible treatment allocations. We will use these data to design the main trial.

**Discussion:**

The ultimate aim of the main trial is to enable clinicians to manage this condition more effectively. If it transpires that ursodeoxycholic acid and early delivery are both safe and effective then steps will be taken to ensure that all women with OC who could benefit from them receives this treatment. Conversely, if one or both the treatments turn out to be ineffective or even harmful, they will be stopped and researchers will work at developing other modes of treatment.

**Trial registration number:**

ISRCTN37730443

## Background

Obstetric cholestasis (OC) is a liver condition unique to pregnancy. It is also referred to as Intrahepatic Cholestasis of Pregnancy (ICP). Pruritus is the characteristic symptom [1,2] accompanied by otherwise unexplained deranged liver enzymes [3-7] and elevated serum bile acid levels [3,7-9]. The itching subsides almost immediately after delivery [1,2,10] and the serum bile acid levels and the liver enzymes normalise within 2–3 weeks of delivery [1,10-14]. Occasionally, a patient might present with atypical symptoms such as jaundice, steatorrhoea, nausea, vomiting, anorexia, hepatomegaly and megalosplenia [15]. It is typically seen in the late second and third trimester [11,16,17] although some studies have reported presentation as early as six to ten weeks gestation [13,18].

Obstetric cholestasis affects between 0.7% and 1% [19]of pregnancies in the UK. It runs a relatively benign course in the mother. The main concern is its association with increased rates of perinatal mortality [1,5,11-14,17,20-24] and spontaneous preterm labour [11-13,17,20,21,23-25]

Most UK obstetricians treat obstetric cholestasis with ursodeoxycholic acid [26] in the belief that it reduces itching although this has not been shown in a suitably sized randomised controlled trial (RCT). Nor has fetal benefit or safety been adequately tested [27,28]. The latest Cochrane review, updated in 2001 [29] included three trials [30-32] involving 56 women comparing ursodeoxycholic acid with placebo. No statistically significant benefit on pruritus, or fetal outcomes was demonstrated. Since then a further trial [28] randomised 130 women diagnosed with obstetric cholestasis to placebo, ursodeoxycholic acid or dexamethasone. The only statistically significant effects in the groups as randomised were beneficial biochemical changes in the ursodeoxycholic acid group. In the subgroup with the highest bile acids at entry, ursodeoxycholic acid was associated with reduced pruritus. Although the only fetal death occurred in the placebo group, there was a non-significant trend towards more meconium in the ursodeoxycholic acid group. The latest guidelines from the RCOG (RCOG Guideline No. 43, January 2006) conclude as follows

"There are insufficient data to support the widespread use of ursodeoxycholic acid outside of clinical trials. Women should be aware of the lack of robust data concerning improvement in pruritus, protection against stillbirth and safety to the fetus or neonate."

Despite this lack of evidence about 4,500 pregnant women are treated with ursodeoxycholic acid each year in the UK and many more worldwide.

Delivery around 37–38 weeks is also widely practiced in the management of obstetric cholestasis on the assumption that it might pre-empt stillbirths [23]. Timed delivery is probably the single most important treatment offered by obstetricians. It is offered whenever the obstetrician believes that the risks of early delivery are less than those of awaiting labour. It is used in fetal growth restriction, pre-eclampsia, preterm and term rupture of membranes, diabetes, post maturity, placenta praevia and placental abruption. It has been evaluated in randomised controlled trials for post maturity, term and preterm rupture of membranes, pre-eclampsia and growth restriction. 75% of respondents in our survey indicated that they would deliver at least some patients with obstetric cholestasis early in the absence of fetal compromise. However, there have been no trials of such intervention and this practice has never been evaluated. There must be the potential for considerable risk of harm, including the fetal death or brain damage from iatrogenic prematurity, or of labour that is more prolonged than it otherwise would have been, and the maternal risks of increased operative delivery.

The RCOG guidelines (RCOG Guideline No. 43, January 2006) conclude as follows: *"Obstetricians should be aware that there are insufficient data to support or refute the popular practice of 'early' (37 weeks of gestation) induction of labour aimed at reducing late stillbirth."*

This is why both interventions need to be evaluated in an adequately powered randomised controlled trial. We are in the process of designing such a trial. Although we have had many indications of willingness to participate in such a trial, we are unable to finalise the sample size calculations without reliable data of the spectrum of disease severity which clinicians are prepared to recruit. To finalise the costings we also need a realistic recruitment rate per centre. We therefore plan "Pilot study for trial of ursodeoxycholic acid and/or early delivery for obstetric cholestasis"

## Methods and Study Design

In this pilot trial we aim to collect data to finalise the design of a factorial trial for the main trial. Ethical approval to conduct this trial was given by the Berkshire Research Ethics Committee (Reference number 08/H0505/7).

### Primary objective

• Measure recruitment to the two factorial interventions separately

### Secondary objectives

• Relate recruitment rates to disease severity

• Estimate a realistic recruitment rate for the definitive trial

• Measure acceptability of randomisation among potential participants offered trial entry

• Measure compliance with each treatment arm

• Measure the completeness of outcome data

• Finalise the design including the sample size calculation for the definitive trial

• Measure medium term (six weeks) maternal and fetal outcomes for the definitive trial.

PITCH is a multi-centre, double-blinded, randomised, controlled, factorial design trial. We will recruit in the three collaborating centres and three other UK centres for eighteen months. Centres will be asked to recruit participants with mild, moderate and severe obstetric cholestasis defined as follows:

Mild: random bile acids ≤ 14 μmol/L, ALT > 100 U/L

Moderate: random bile acids 15–40 μmol/L

Severe: random bile acids > 40 μmol/L

There are two comparisons:

### Comparison A – Ursodeoxycholic acid versus placebo

Investigational Medicinal Product (IMP) will be started at 500 mg bd. The dose will be increased in increments of 500 mg per day every 3–14 days if there is no biochemical or clinical improvement until a maximum of 2 grams per day is reached. Criteria for increasing the dose will be no improvement in itching or a rise in serum Alanine Transaminase (ALT) or bile acids. If there is no response to this dose, the dose can be increased up to 3 grams per day at the discretion of the treating clinician. The decision to increase the dose will always be at the discretion of the treating clinician.

#### Control group

Placebo capsule will be increased according to the same regime. In both control and intervention groups, participants will be blind to their group allocation.

Ursodeoxycholic capsules 250 mg and matching placebo are manufactured and supplied by [name] GmbH. Packaging and labelling to provide blinded treatment packs is carried out in the production unit of the pharmacy department,, Queen's Medical Centre (QMC), Nottingham University Hospitals NHS Trust, UK. Supplies will be packed in an approved container and labelled with a single panel label. Subject name, randomisation number and date of dispensing will be added to the label as part of the dispensing process. The co-ordinating pharmacy will add a further label to each container to identify principal investigator, site address and contact telephone number.

### Comparison B – Early versus late delivery

Early planned delivery at between 37^+0 ^and 37^+6 ^weeks gestation by final agreed estimated date of delivery (EDD) or await spontaneous labour. For this part of the study, only participants <38^+0 ^weeks will be eligible. In early delivery/await spontaneous labour group, participants will be aware of group allocation.

We recognise that there is now evidence to support the induction of even uncomplicated pregnancy by 40^+10 ^weeks. Obstetricians are permitted to induce participants in the "await spontaneous labour" group from 40^+0 ^weeks, or as clinical needs dictate.

### Recruitment

Six UK centres will participate in the trial. Any pregnant women with itching and either a random serum bile acid level over 14 μmol/L, or an ALT over 100 U/L, between 24^+0 ^and 40^+6 ^weeks who has been diagnosed with obstetric cholestasis will be approached by a member of the clinical team and invited to participate in the trial. After seeking verbal consent, the potential participant will be referred to the local investigator. This local investigator may be a consultant, obstetrician in training or midwife according to local preferences. This person will give detailed information (verbal and the appropriate participant information sheet) regarding the purpose of the trial and procedures involved. If needed, the usual hospital interpreter and translator services will be available to assist with discussion of the trial, the participant information sheets, and consent forms but the consent forms and participant information sheets will not be available printed in other languages. Potential participants will be given adequate time to consider participation. Participants recruited at or after 38^+0 ^will only be eligible for ursodeoxycholic acid/placebo comparison. It will be explained to the potential participant that that entry into the trial is entirely voluntary and that their treatment and care will not be affected by their decision.

We will record all use of ursodeoxycholic acid, other drugs and labour induction for obstetric cholestasis outside the trial in participating centres.

### Inclusion criteria

• Itching in pregnancy

• 24^+0 ^to 37^+6 ^weeks pregnant eligible for both comparisons (38^+0 ^to 40^+6 ^weeks eligible for ursodeoxycholic acid/placebo comparison only)

• Bile acids > 14 μmol/L and/or ALT > 100 U/L

• Age 18 – 55 years

• Clinician responsible for care uncertain whether ursodeoxycholic acid or early delivery is beneficial

• Patients who otherwise fulfil the recruitment criteria, but incidentally have either hepatitis C, or cholelithiasis, or both, are eligible and may be included

• Women with multiple pregnancies who are otherwise eligible may be included in the ursodeoxycholic acid/placebo comparison only

• Willing to participate in the trial and able to give informed consent

### Exclusion criteria

• Dermatological and allergic pruritus with normal liver enzymes

• Other causes of pruritus and deranged liver enzymes (except hepatitis C and cholelithiasis)

• Hepatitis A, hepatitis B, pre-eclampsia, primary hepatic disorders, alpha-1 antitrypsin deficiency and current medications causing deranged liver enzymes

• Women unable or unwilling to consent

• Known lethal fetal anomalies

• Allergy to any component of the ursodeoxycholic acid or placebo capsules

### Consent

All participants will provide written informed consent. The consent form will be signed and dated by the participant before they enter the trial. The investigator will explain the details of the trial and provide the appropriate participant information sheet, ensuring that the participant has sufficient time to consider participation. The investigator will answer any questions that the participant has concerning study participation. One copy of the consent form will be kept by the participant, one will be kept by the investigator, and a third will be retained in the participant's hospital records. Should there be any subsequent amendment to the final protocol, which might affect a participant's participation in the trial, continuing consent will be obtained using an amended consent form which will be signed by the participant. The process for obtaining participant informed consent will be in accordance with the Research Ethics Committee (REC) guidance, and Good Clinical Practice (GCP) and any other regulatory requirements that might be introduced.

### Randomised procedure

After taking an informed consent, pre-randomisation baseline data will be collected (see additional file 1). The recruiting investigator (researcher, clinician or midwife) will ensure that a blood sample has been taken for a bile acid and ALT level. If convenient a fasting sample will be taken for bile acid. Participants will also be asked to consent for placenta and/or cord blood sample to be collected at delivery for DNA and molecular studies.

Randomisation will be via the Nottingham Clinical Trials Unit (NCTU) using a web-based database and randomisation system. In each centre, the recruiting investigator will have a username and password. S(he) will log on to the trial website that hosts the trial database, confirm that the participant eligibility criteria are all met and enter an agreed minimum amount of registration data about the participant and centre before randomisation is possible. The computer will then issue a participant study identification number which will be the unique identifier for the trial participant. Randomisation will be stratified by the trial centre only.

Participants will be randomised and allocated to ursodeoxycholic acid/placebo and/or early planned delivery/await spontaneous delivery (if < 38^+0 ^weeks). The details of the comparisons offered at each gestational age will differ as follows:

• 24^+0 ^– 34^+0 ^weeks:

• Offer ursodeoxycholic acid versus placebo immediately

• If still undelivered at 34^+1 ^– 37^+6 ^weeks, offer 'early delivery' versus 'await spontaneous labour'

• 34^+1 ^– 37^+6 ^weeks

Offer full factorial trial. Participants may choose one or the other comparison or both.

• Ursodeoxycholic acid versus placebo

• Early delivery versus await spontaneous labour

• ≥ 38^+0 ^weeks

• Offer ursodeoxycholic acid or placebo only

After randomisation to ursodeoxycholic acid/placebo comparison, an online prescription form will be generated. The investigator will download and print this prescription form. The participant is asked to collect the trial IMP/placebo from the pharmacy. The local pharmacist will select the pack with the appropriate number and issue this to the participant. The investigator, pharmacist and the trial participant will be blind to group allocation.

In early delivery/await spontaneous labour group, the investigator and the trial participant will be aware of group allocation. Obstetricians are permitted to induce participants in the 'await spontaneous labour' group from 40^+0 ^weeks, or as clinical needs dictate.

### Weekly follow-up

After randomisation, participants will be seen weekly by the researcher, a research midwife or their clinician as appropriate to local conditions in the antenatal clinic or day assessment unit. The participant will be asked to complete the compliance progress data form (see additional file 2) and the visual analogue itching scale. Blood samples will be collected weekly for ALT and bile acids and research blood samples will be collected for women who have consented. The frequency of fetal monitoring will depend on the local preferences. Each centre will define its monitoring regime.

The following data will be collected at weekly visit:

• Compliance progress data form

• Visual analogue itching scale

• Blood sample for serum bile acid and ALT level

• Use of other medications being taken by the participant

• Any adverse events

### Follow-up at or immediately after delivery

If the participant has consented to the optional genetic study, research samples (cord blood and placental sample) will be collected by the researcher, clinician or midwife as locally appropriate at the time of delivery. After delivery 'Outcome at hospital discharge' form (see additional file 3) will be completed by the local investigator.

### Follow-up at six weeks post delivery

Study participants will be seen at six weeks post delivery in the antenatal clinic or day assessment unit by the investigator. The 'Outcome at six weeks post delivery' form (see additional file 4) will be completed during this visit. The visual analogue itching scale will be scored and a blood sample will be collected for serum bile acid and ALT level. Research samples will be collected if consented (figure 1).

**Figure 1 F1:**
[figure not shown]
**Flow of trial participants from recruitment to six weeks follow-up after delivery**.

### Withdrawal from the trial

Participants may withdraw from the trial either at their own request or at the discretion of the treating clinician. They will be made aware that this will not affect their future care. Participants will be made aware via the participant information sheet that should they withdraw, the data collected to date cannot be erased and may still be used in the final analysis. Participants who withdraw from treatment (either ursodeoxycholic acid or placebo; early delivery or await spontaneous labour) will remain in the studies for follow-up and analysis. Even those who decline to complete special follow-up arrangements will be asked to allow pregnancy outcome data to be included in the analysis and consent will be taken for the same. Those participants who wish to withdraw and are not yet randomised can be replaced but participants who withdraw after randomisation will not be replaced.

### Maintenance of randomisation codes and procedures for breaking code

The placebos used will be similar in appearance to the IMP capsules. They will be provided in bottles. There will be no marking on the capsule to suggest whether it is a placebo or IMP. If the participants clinical condition deteriorates (worsening of itching, increasing bile acids and/or ALT), the patients clinician can make the decision for delivery as clinical needs dictate. The treatment code will not be broken in such cases. In cases of serious adverse event (SAE), the event shall be reported immediately of knowledge of its occurrence to the chief investigator.

### Endpoints

#### Primary endpoint

• Total recruitment rate per 1000 deliveries/annum

• Total recruitment rate per eligible women

#### Secondary endpoint

• Recruitment for the three subgroups of mild, moderate and severe disease separately

#### Safety endpoints

It is not possible to define a predetermined safety endpoint for this trial. Both treatments are in common use. All adverse events will be reported to the Data Monitoring and Ethics Committee (DMEC).

### Statistics

We have estimated that a provisional sample size for the main factorial trial will be 1498 women (749 per group). This would give 80% power, alpha 0.05, to show a reduction in the primary composite endpoint (fetal death or severe morbidity) from 6% to 3%. However, detailed power calculations are not possible without measuring the clinical spectrum of likely recruits to such a trial.

In the pilot phase we will develop and pilot the definitive trial as follows:

At the launch meeting, collaborators will register their current obstetric cholestasis treatment policies. All collaborators will also agree to register all cases of obstetric cholestasis in their centre. Collaborators will then return to their centres and recruit to the trial for eighteen months. During this time each centre will receive three site visits from the research fellow, as well as regular newsletters, email and phone contacts. At the end of the pilot recruitment period each centre will produce the following data:

• Total number of deliveries

• Number of participants identified with obstetric cholestasis in each severity band

• Number recruited to the full factorial trial, and to the ursodeoxycholic acid/placebo or the early delivery/await spontaneous labour comparison only

• Number treated for obstetric cholestasis outside the trial

• Compliance with treatment and outcome data as for the definitive trial.

In the pilot phase we will recruit in each centre for eighteen months. We recognise that strictly the most efficient way to measure the recruitment rate in each centre would be to recruit until a fixed number of participants, say ten, had been enrolled. However, given the sunk costs of setting up each centre, there are little extra costs from continuing each centre beyond such a number. The target sample size of the pilot of approximately ninety participants (equivalent to fifteen particpants per centre over eighteen months, ten per centre per annum) has been chosen to allow a reasonably precise estimate of the various parameters for the main trial.

1. Mean recruitment rate per centre over eighteen months. By weighting recruitment by the size of each unit we will model predicted recuitment for the proposed centres in the main trial.

2. The proportion of moderate/severe cases. If this is much below 50% the main trial will probably not be feasible. Example 45/90 50% severe cases would have 95% CI of 39–61%.

3. The proportion recruiting to both comparison groups. Example 80/90 89% 95% CI 81–94%

We cannot at this stage specify exactly what levels for each parameter would make the main trial feasible since to some extent they can be traded off against each other. For example a relatively low level of severe cases recruited can be traded off against a higher than expected overall recruitment rate. The following broad parameters are suggested.

#### Example 1

Recruitment rate per centre of 10 per annum, of which 2/3 moderate or severe cases, >80% enter both comparison arms, >95% compliance with ursodeoxycholic acid/placebo comparison and >70% compliance with early delivery/await spontaneous labour comparison. We would plan to recruit for the main trial in 50 centres over three years. We believe that this would probably be feasible within the UK

#### Example 2

Recruitment rate per centre of 5 per annum. Same proportion of severe cases and same compliance levels would require a trial with 100 centres over three years. This would probably be too much for UK only centres. We would consider collaboration with another one or two European Union countries on a similar trial design.

#### Example 3

Recruitment rate per centre of less than 5 per annum. Only 1/3 moderate or severe. The main trial would not be realistically feasible. Similarly if recruitment to either the ursodeoxycholic/placebo comparison or to the earlydelivery/await spontaneous labour comparison was below 50% we would probably drop the relevant comparison from the main trial.

We have intentionally not drawn hard and fast rules for going ahead or not with the main trial. At the end of the pilot we will call a collaborators meeting of representatives of about 50 UK centres at the RCOG at which the pilot data will be presented, a range of trial designs will be presented, feasibility will be discussed and a final decision will be taken.

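### The centre counts in Examples 1 and 2 both come to 1,500 women, the uninflated main-trial size, so the entry and compliance levels in those examples change neither power nor centres

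*Protocol article*

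**What the plan says.** The Statistics section gives, for the main trial: "provisional sample size for the main factorial trial will be 1498 women (749 per group). This would give 80% power, alpha 0.05". The target is a fall in the composite of fetal death or severe morbidity from 6% to 3%. The section adds that "detailed power calculations are not possible without measuring the clinical spectrum of likely recruits to such a trial".

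Example 1 assumes 10 recruits per centre per year and lists ">80% enter both comparison arms, >95% compliance with ursodeoxycholic acid/placebo comparison and >70% compliance with early delivery/await spontaneous labour comparison". It then says: "We would plan to recruit for the main trial in 50 centres over three years". Example 2 halves the recruitment rate, keeps the same compliance levels and arrives at 100 centres over three years, with the comment: "This would probably be too much for UK only centres".

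The same section says that the parameters can be traded off against each other, that the levels are only broad suggestions, and that no firm rule for proceeding has been set. A collaborators' meeting will decide after the pilot.

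**The concern.** Each example presents a package: a recruitment rate, a share entering both comparisons, a compliance level for each comparison, and the number of centres that results. A reader will take the centre count as following from the whole package. In fact it follows from the recruitment rate alone. Women who do not enter the delivery comparison add nothing to its sample size, and women who are not delivered as allocated narrow the difference between arms under intention to treat. Neither effect appears in the 50 or the 100 centres.

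These examples are the only quantified benchmarks that the article offers for the collaborators' meeting. If the pilot lands on Example 1, the meeting could judge 50 centres sufficient when the delivery comparison would have less than 80% power, possibly much less.

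**Working it through.** **Inputs (all from the Statistics section).** 6% v 3%; 80% power; alpha 0.05 (two-sided reproduces the figure); 749 per group. Example 1: 10 per centre per year, 50 centres, 3 years; floors of 80% entering both comparisons, 95% drug compliance and 70% delivery compliance. Example 2: 5 per centre per year, 100 centres, 3 years.

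**1. Reproduce the stated size.** With pooled variance under the null and p̄ the mean of p1 and p2,

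n per group = [1.960·√(2p̄(1−p̄)) + 0.8416·√(p1(1−p1) + p2(1−p2))]² / (p1−p2)²

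= [1.960·√0.08595 + 0.8416·√0.0855]² / 0.03² = 748.4, rounded up to 749. Total 1,498. The match is exact, so the figure contains no allowance for non-entry, non-compliance or dropout.

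**2. Reproduce the centre counts.** Example 1: 10 × 50 × 3 = 1,500. Example 2: 5 × 100 × 3 = 1,500. Both are the uninflated size.

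**3. Power at Example 1's floors.** Power = Φ{[|p1−p2|·√n − 1.960·√(2p̄(1−p̄))] / √(p1(1−p1) + p2(1−p2))}, with n per arm = 1,500 × entry share / 2.

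Entry: under Randomised procedure, women from 34+1 to 37+6 weeks may choose either comparison or both, so a recruit who is not in both is in one. If 80% enter both, the delivery comparison keeps 80% of recruits (the rest enter the drug comparison only), 90% (the rest divide evenly) or 100% (the rest enter delivery only).

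Dilution: the article does not say which arm the 30% non-compliance falls in, so each case is shown. For example, if 30% of the early arm is not delivered early, its rate is 0.7 × 3% + 0.3 × 6% = 3.9%.

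| Delivery comparison | Rates | 750 per arm (100%) | 675 per arm (90%) | 600 per arm (80%) |
|---|---|---|---|---|
| 6% v 3% already as randomised | 6.0 v 3.0 | 80.1% | 75.8% | 70.8% |
| Non-compliance in early arm | 6.0 v 3.9 | 46.6% | 42.8% | 38.8% |
| Split evenly between arms | 5.55 v 3.45 | 50.1% | 46.1% | 41.9% |
| Non-compliance in await arm | 5.1 v 3.0 | 54.1% | 49.9% | 45.4% |
| Each arm only 70% compliant | 5.1 v 3.9 | 20.1% | 18.5% | 16.9% |

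Drug comparison, 95% compliance in the active arm (6.0 v 3.15): 75.3% with 1,500 women.

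**4. Women and centres for 80% power in the delivery comparison at 0.7 net separation.**

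| Non-compliance in | Per arm | In the comparison | Centres (÷30) | Recruits at 80% entry | Centres (÷30) |
|---|---|---|---|---|---|
| Await arm | 1,383 | 2,766 | about 92 | about 3,458 | about 115 |
| Early arm | 1,674 | 3,348 | about 112 | 4,185 | about 140 |

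The divisor is 10 per year × 3 years = 30 women per centre. The evenly split case (1,529 per arm, 3,058 in all) lies between the two.

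**The case against.** The strongest reply is that the article never says the 3-point difference is a full-compliance effect. Read as the difference expected between the randomised groups, it already contains whatever non-compliance is foreseen, and only entry matters: 71% to 80%. This stands, and it is why no single power figure can be attached to Example 1. A reader might infer that the delivery comparison simply has 40-50% power. The documents do not support that as a fact, because it needs proportional dilution of a full-compliance effect. The as-randomised reading has a difficulty of its own, however. One effect serves both comparisons although their compliance floors differ, so the full-compliance differences would have to be about 3/0.95 = 3.2 points for the drug and 3/0.70 = 4.3 for delivery. The article gives no basis for that.

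A reader might also take 20% off both comparisons. That cannot be right, since a woman not in both is in one. If all the loss falls on delivery, the drug comparison keeps its 1,500. A loss mainly on delivery is plausible, because Recruitment and Inclusion criteria confine women at 38+0 weeks or later, and those with multiple pregnancies, to the drug comparison.

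The levels are floors. At 80% compliance in the early arm (6.0 v 3.6), power at full entry is 58%, which is better but still short of 80%. It is also unclear what counts as non-compliance in the await arm, since induction is permitted there from 40+0 weeks or when clinically needed.

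Finally, the size is called provisional, no firm rule for proceeding is set, and Secondary objectives already include measuring compliance and finalising the sample size. So it would be wrong to say that the plan fixes the main trial at 1,500 or commits to launching it. This lowers the severity. It does not remove the point: the reason given for deferring detailed power calculations is the clinical spectrum of recruits, and the examples pair explicit entry and compliance levels with a centre count that ignores them.

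**Conclusion.** The point holds as a should-fix. The 1,498 is correctly calculated, but the 50 and 100 centres are that number divided by the recruitment rate, with no allowance for the entry and compliance levels listed beside them.

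On the reading most favourable to the plan, the delivery comparison has about 71% power if all the non-entry falls on it, 76% if the non-entry is shared evenly and 80% if none falls on it. If 3 points is the full-compliance effect and 70% is the net separation, power is about 47-54% at full entry and 39-45% at 80% entry. If each arm is only 70% compliant, it is about 17-20%. The drug comparison, with 95% compliance in the active arm and full entry, has about 75%.

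A reader might go further and conclude that Example 1 needs well over 100 centres, and so is infeasible by Example 2's own standard. The documents do not establish that. The 92 to 140 centres depend on the full-compliance reading, on 0.7 net separation and on where the non-entry falls. They show that the conclusion on feasibility is sensitive to something the article leaves unstated.

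**What to change.** In the Statistics section:

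1. State whether 6% v 3% is the effect as randomised, already allowing for non-compliance, or the effect under full compliance.
2. State that 1,498 women and 80% power hold only if every recruit enters the comparison concerned.
3. Say what the 70% delivery compliance measures: one arm, each arm or the net separation between arms.
4. For each example, give power and centres separately for the drug and delivery comparisons at the listed entry and compliance levels, as a range with the assumptions shown. On the full-compliance reading at 0.7 net separation, for instance, 80% power for delivery needs about 2,766-3,348 women in that comparison. That is 92-112 centres at 10 per year for three years, and up to about 115-140 if only 80% of recruits enter it.
5. Present this table at the collaborators' meeting and replace the assumed values with pilot estimates once they are available.

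The cost is some rewording and one small table. The pilot's target of about ninety women, its endpoints and its conduct do not change, and it already plans to collect entry to each comparison and compliance. The stated feasibility may look less favourable.
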